### Secondary outcome measurements

#### Exercise capacity

The 6MWT will be performed at baseline, 4th week, 8th week, and 12th week. The walking distance in meters within 6 min will be measured according to the American Thoracic Society guidelines [34]. The test will be done at least 2 h before the CPX test. An assistant blinded to the study group will read standardized, scripted instructions to each patient. Patients will be instructed to walk as far as possible and allowed to stop as often as they need if they are fatigued. The 6MWT is one of the most common instruments for measuring changes in exercise tolerance following exercise-based interventions in patients with CHF [35].

The TUGT will be performed at baseline, the 4th week, 8th week, and 12th week. It appears to be a reliable and valid functional measurement in patients with CHF, and is frequently used in rehabilitation settings as a measure of balance and mobility [36]. Patients are required to stand up from a 45-cm-high chair, walk 3 m at a comfortable pace, turn 180°, return to the starting point, and sit again. This test will be timed with the use of a standard stopwatch by a research assistant blinded to the treatment arm.

#### Exercise self-efficacy

Exercise self-efficacy will be self-assessed by the SEE-C at baseline, the 4th week, 8th week, and 12th week. The participants will be instructed to listen to nine different situations, and then to choose an option from 0 (not confident) to 10 (very confident) that represents their perception of confidence regarding engaging in regular exercise. The scale will be scored by summing the numerical ratings for each response and dividing the total by the number of non-missing responses. The mean scores for the self-efficacy of exercise will range from 0 to 10, with the higher scores representing greater exercise self-efficacy. A validated Chinese version of the SEE-C will be employed in this trial [37].

#### Generic quality of life

Generic quality of life will be self-assessed by the EQ-5D-5 L questionnaire at baseline, the 4th week, 8th week, and 12th week. This questionnaire has been used previously to measure health status in patients with heart failure [38, 39]. The EQ-5D-5 L questionnaire measures five items (mobility, self-care, usual activities, pain/discomfort, and anxiety/depression), with each item including five levels: no problems, some/moderate problems, and severe/extreme problems. In addition to the five health-state items, the EQ-5D also contains a Visual Analog Scale, a graph representation similar to a thermometer that ranges from 0 (worst imaginable health state) to 100 (best imaginable health state). It has been used previously to measure health status in patients with heart failure. A validated Chinese version of EQ-5D-5 L will be employed in this trial [40].

Subjective health will be self-assessed by the GRC at baseline, the 4th week, 8th week, and 12th week. The GRC will use a single item that compares current subjective health with previous subjective health at baseline. The response scale will range from − 7 (much worse) over 0 (no change) to 7 (much better) [41].

#### Hallmark symptoms of dyspnea and fatigue

Dyspnea and fatigue will be self-assessed by the PFSDQ-M at the baseline, 4th week, 8th week, and 12th week. The PFSDQ-M is comprised of 40 items divided into three components: dyspnea, fatigue, and activity. The activity domain evaluates changes in ten activities beginning at the point the patient first developed CHF: brushing/combing hair; putting on a shirt; washing hair; showering; raising arms overhead; preparing a snack; walking 10 feet; walking on inclines; walking on bumpy terrain; and climbing three stairs. The dyspnea component evaluates dyspnea for frequency during the preceding month; intensity of dyspnea on most days, the present day, and with usual activity levels (rated on a scale from 0 to 10); and intensity of dyspnea when the above-mentioned ten activities are performed (rated on a scale from 0 to 10). The fatigue component evaluates fatigue for the same items as the dyspnea component. Higher scores indicate more severe symptoms. The PFSDQ-M is validated and is reliable in patients with CHF. A validated Chinese version will be employed in this trial [42].

#### Depression status

The HADS will be self-administered at the baseline, 4th week, 8th week, and 12th week to measure the presence of depression and anxiety. It has been shown to be a valid and reliable measure of the severity of emotional disorders and is used in general hospital practice. Participants will be instructed to choose one response from the given answers that best describe their current feelings. The HADS is a 14-item self-report screening scale originally developed to indicate the possible presence of anxiety and depressive states in the setting of a medical outpatient clinic.

#### Cardiac function

Echocardiography: left ventricular ejection fraction (LVEF) will be assessed by echocardiography at baseline and at the 12th week. Each participant will undergo an initial resting three-dimensional, multi-view echocardiogram before the exercise program is initiated. Another echocardiogram will be taken upon completion of the program. LVEF will then be computed by dividing the stroke volume by the end-diastolic volume. In addition, other parameters related to diastolic/systolic/valvular status will also be collected.

A 12-lead ECG and Holter 24-h ECG will be conducted at baseline and at the 12th week. Data will be collected on a variety of parameters reflecting cardiac function such as rhythm, heart rate, duration of PQ interval (ms), QRS interval (ms), QT interval (ms), and QTc interval (ms), presence of second or third degree atrioventricular block, bundle-branch configuration, and tachycardia with narrow or wide QRS or delta waves. In addition, subjects’ autonomic nervous system function will be assessed using heart rate variability.

#### Levels of prognostic biomarkers and inflammatory indicators

Blood samples will be collected at baseline and 12 weeks to measure the levels of prognostic biomarkers (NT-proBNP) and inflammatory mediators (hsCRP). NT-proBNP and hsCRP will be analyzed by the GPHCM laboratory. The NT-proBNP is correlated with risk for all-cause, cardiac, and pump-failure mortality, and hsCRP is elevated in CHF as the disease progresses [6].

#### Hospitalization-related outcomes and medication usage

Hospitalization-related outcomes: all instances of hospitalization will be recorded throughout the study period and made accessible to an independent adjudication panel consisting of three experienced cardiologists. They will ascertain whether or not the reported events are heart failure-related.

Medication usage: usual medical management as well as concomitant medications will be documented in detail by cardiologists. In addition, concomitant medications must be recorded in participants’ exercise logs. Medical records, interview data, and automated utilization data will also be used to document patients’ use of healthcare throughout the study period.

#### MACEs

The MACEs are the most commonly used composite endpoints in cardiovascular research, and thus will be recorded throughout the study period [43]. MACE components in our study include events of death, myocardial infarction, stent thrombosis, percutaneous coronary interventions, coronary artery bypass graft surgery, and stroke.

### Physical activity level

The physical activity levels of all participants will be measured in two ways: (1) step counts, and (2) self-reported questionnaires. The step count will be measured using an accelerometer (Garmin Vivofit) that we will provide to each participant, both in the intervention and control groups. Participants will be required to wear the step count all day throughout the study period. Patients will return the step counts, and the ensuing data will be downloaded by research assistants. In addition, physical activity will be self-reported using the validated Chinese version of the International Physical Activity Questionnaire short-form [44] at the baseline, 4th week, 8th week, and 12th week.

### Safety

An independent Data and Safety Monitoring Committee will evaluate the progress of the study and assess the safety data, as requested during the study. Adverse events (AEs) will be defined as any undesirable experience participants endure during the trial period, regardless of whether or not it is associated with the intervention. Participants will be instructed to report AEs to the research team at any time, and a research nurse will monitor participants for potential occurrences of AE. All details of AEs, such as time of occurrence, severity, management, and causality to the intervention will be recorded on Case Report Forms (CRFs). All AEs will be followed up from the date they are brought to the investigator’s attention until resolution. Severe AEs must be reported to both the GPHCM Data and Safety Monitoring Committee and the GPHCM Ethics Committee within 24 h. Severe AEs will be defined according to the International Conference on Harmonization guidelines [45]: any adverse event will be regarded as serious if it results in death, is life-threatening, requires hospitalization or prolongation of existing hospitalization, or results in persistent or significant disability or incapacity.

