### Trial management and quality control

The management structure is comprised of principle investigators (PIs) including [name], [name], and [name], a Trial Management Group, a Data Monitoring Committee, and a Trial Steering Committee.

The Trial Management Group is responsible for the day-to-day delivery and for conducting the trial. It will be comprised of a project manager as well as a cardiac rehabilitation team and investigators from the GPHCM. The Trial Management Group will meet weekly to discuss trial progress. The project manager will have a face-to face meeting with the PIs every other week.

The role of the Data Monitoring Committee is to review safety and efficacy data and to make recommendations to the Trial Steering Committee. It will be comprised of four fully independent members: one chairman, one senior biostatistician, one cardiologist, and one *Baduanjin* expert from the GPHCM. The Data Monitoring Committee will meet once, prior to the start of patient recruitment, and at least once a year for those years in which patients are involved in exercise sessions.

The responsibilities of the Trial Steering Committee are to approve the main study protocol and any amendments, to monitor and supervise the trial, steering it towards its specific and overall objectives, to review relevant information from other sources, to approve and comment on project deliverables, to consider the recommendations of the Data Monitoring Committee, and to resolve any problems brought up by the Trial Management Group. It will be comprised of one independent chairman, [name], [name], [name], [name], and four other independent members including at least one patient and a public involvement representative. Responsibility for calling and organizing the Trial Steering Committee meetings lies with the PIs. The Trial Steering Committee will meet at least annually, and more frequently as needed. Representatives of the Data Monitoring Committee are to be invited to all Trial Steering Committee meetings.

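### The 24-hour reporting list has no place for a medically important exercise-related event without admission or lasting disability, and the independent committee's only scheduled review is at least yearly

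*Protocol article*

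**What the plan says.** The Safety section sets the expedited rule: "Severe AEs must be reported to both the GPHCM Data and Safety Monitoring Committee and the GPHCM Ethics Committee within 24 h". The next sentence gives the class its content: "Severe AEs will be defined according to the International Conference on Harmonization guidelines". The criteria follow: "any adverse event will be regarded as serious if it results in death, is life-threatening, requires hospitalization or prolongation of existing hospitalization", and finally "or results in persistent or significant disability or incapacity". That makes four criteria, and none is specific to exercise.

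The same section treats severity as an attribute of every adverse event: "All details of AEs, such as time of occurrence, severity, management, and causality to the intervention will be recorded on Case Report Forms". It also says how events are picked up: "Participants will be instructed to report AEs to the research team at any time, and a research nurse will monitor participants". All of them are followed until they resolve.

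Committee review is described in two places. Under Safety, a Data and Safety Monitoring Committee is to "assess the safety data, as requested during the study". Under Trial management and quality control, a Data Monitoring Committee meets once before recruitment and then "at least once a year for those years in which patients are involved in exercise sessions".

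**The concern.** Safety is one of the trial's stated aims. The patients are in NYHA class II or III. Intervention patients are encouraged to exercise at home with a picture brochure, and coach-led classes are optional. The events that say most about harm from such a programme need not lead to admission or lasting disability. Under the text as written, those events fall outside the 24-hour rule.

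The committee is the body charged with reviewing safety data and advising the Trial Steering Committee. Each patient's exercise phase lasts 12 weeks, so a yearly interval is more than four times one patient's exposure (52/12 = 4.3). A pattern of such events could build up across many patients before the independent body has any scheduled occasion to look at it.

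The label adds a smaller problem. The rule that decides what is expedited uses the word severe for a class defined by seriousness, while severity is graded separately on the same form.

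**Working it through.** The plan gives no figure on this point, so there is none to reproduce. The check has two parts.

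**1. Which events reach the committee, and how**

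| Event | Within 24 h? | Other stated route to the committee |
|---|---|---|
| Death | yes | – |
| Life-threatening event, including a life-threatening arrhythmia | yes | – |
| Admission or prolonged admission | yes | – |
| Persistent or significant disability or incapacity | yes | – |
| Syncope, fall or non-life-threatening arrhythmia during exercise, without admission or lasting disability | no | Review on request (Safety; no requester or trigger named), or the meeting held at least yearly (Trial management) |

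**2. How late a scheduled review could be**

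Inputs from the article: a 12-week exercise phase, a 2-week pre-phase and at least one meeting a year. Assumptions: uniform accrual over A weeks, and a first routine meeting 52 weeks after the first enrolment. L is the time a patient needs to finish: 12 weeks, or 14 if the pre-phase is counted.

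Share of patients enrolled by the meeting who have finished, for A ≥ 52:

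- (52 − L)/52
- L = 12: 40/52 = 77%
- L = 14: 38/52 = 73%

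Share of all patients finished at that meeting, for A ≥ 52: (52 − L)/A.

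| A (weeks) | L = 12 | L = 14 |
|---|---|---|
| 52 | 77% | 73% |
| 78 | 51% | 49% |
| 104 | 38% | 37% |
| 156 | 26% | 24% |

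More than half of all patients have finished only if A is below 2 × 40 = 80 weeks (L = 12) or 2 × 38 = 76 weeks (L = 14). The share among those enrolled so far does not depend on A once A is 52 or more.

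For a single event, suppose meetings are strictly yearly and no review is requested. The mean wait to the next meeting is 52/2 = 26 weeks. If the event falls uniformly within the patient's 12 weeks, 6 weeks remain on average. The chance that the patient's own course ends before the next meeting is then 1 − 6/52 = 88%.

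**The case against.** The strongest answer is that no adverse event is lost. The definition covers any undesirable experience, related or not. Patients can report at any time, a research nurse monitors them, and time, severity, management and causality are recorded. Every event is followed to resolution. The Trial Management Group meets weekly, and intervention patients have consultations at weeks 4, 8 and 12 that cover symptoms and signs during exercise. A reader might infer from the closed list that these events go unnoticed. The documents do not support that: the gap concerns the committee and the ethics committee, not the study team. What remains is that the management group includes the cardiac rehabilitation team, which delivers the programme, and so is not an independent reviewer.

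Second, yearly is a minimum, and the Safety section also allows review on request. This stands, and the conclusion is worded to allow for it. The article names no trigger for a request, but a committee charter or the full protocol may, so that silence is not held against the plan.

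Third, the definition refers to a cited guideline. Whether the four criteria shorten that guideline's list cannot be judged from the article. The point rests only on the list as printed.

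Fourth, the severe/serious wording is resolved by the definition that follows it. This also stands: on its own it is a clerical correction. Nor does it muddle any planned table, because the Quantitative data analysis section tabulates adverse events by group and plans no breakdown by severity.

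**Conclusion.** The point holds in a limited form. The printed 24-hour list has four criteria and leaves out medically important exercise-related events without admission or lasting disability. For these the article states no expedited route to the independent committee. Unless a review is requested, the first scheduled occasion is a meeting held at least yearly. About 77% of the patients enrolled by a week-52 meeting would then have finished (73% counting the pre-phase).

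That percentage assumes uniform accrual over 52 weeks or longer and a first meeting at week 52; neither is in the article. A reader might take it to mean that most of the trial's patients would be through the programme by then. That does not follow: with accrual over 104 weeks, 38% of all patients would have finished.

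How often such events will occur is not given, so the expected number cannot be stated. The change is worth making because it alters which events the committee hears about promptly, at little cost.

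**What to change.** In the Safety section:

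- Call the expedited class serious, and keep severity as the separate grade on the Case Report Form.
- Add to the 24-hour list adverse events that the investigator judges medically important, even without admission.
- Keep the review on request, and reconcile it with the at-least-yearly meeting under Trial management and quality control.
- Use one name for the committee in both sections, or say that there are two bodies and what each does.

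A cumulative adverse event listing sent to the committee at set enrolment milestones would shorten the wait further. It is optional, one of several workable arrangements, and should add to the on-request route rather than replace it.

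The cost is a change of wording and a few more expedited reports. The information needed is already recorded on the Case Report Form.

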### Qualitative data

Participants who are randomized to the RCT intervention group will be selected for the qualitative study. A purposive sampling strategy will be used based on maximum variation principals regarding age, gender, severity of CHF, education level, working status, whether having grandchildren, and the preliminary results of the pilot study. Participants will be recruited until saturation is reached, and the sample size is expected to be between 15 and 20. Data saturation is defined as no new information having been obtained from further interview. All participants will provide additional informed consent before taking part in this qualitative study.

Two female research assistants will conduct the interviews: one a nurse in the department of cardiology, and a resident physician with a background in cardiology. Both assistants will receive education and training in conducting interviews. They will not be part of the BESMILE-HF research team; however, the BESMILE-HF study research staff will inform them of the purposes of this qualitative study.

The semi-interviews will be conducted in a quiet room in the GPHCM or at patients’ homes, depending on patient preference. The duration of the interviews will range from 1 to 1.5 h, and all will be recorded and transcribed verbatim. An interview guide will be developed based on a review of the relevant academic literature, and will be piloted before use. During the interviews, participants will be encouraged to speak freely about their experiences with and perspectives on the entire BESMILE-HF program, motivating and inhibiting influences of the program, and suggestions for improvement. Subsequently, they will primarily be asked about their preferences, attitudes, use, abilities, and challenges regarding *Baduanjin*. All questions will be open-ended, and follow-up questions will be used to gain a deeper understanding of areas that appear essential for each individual.

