This study (BESMILE-HF) aims to assess the efficacy, safety, and acceptability of the addition of the BESMILE-HF program to usual medications for CHF patients in China [23]. The primary hypothesis is that the BESMILE-HF program plus usual medications (as received by participants in the “intervention group”) compared with usual medications alone (as received by participants in the “control group”) can improve exercise capacity, measured as peak oxygen consumption (VO_2_) from a cardiopulmonary exercise test (CPX); also measured as quality of life based on total scores from the Minnesota Living with Heart Failure Questionnaire (MLHFQ) at 12 weeks (co-primary outcomes). Secondary objectives are to evaluate the effect of the BESMILE-HF program on: exercise performance, exercise self-efficacy, overall quality of life, hallmark symptoms such as dyspnea and fatigue, depression, cardiac function, levels of prognostic biomarkers/inflammatory indicators, hospitalization, use of medications and major adverse cardiac events. Other objectives are to explore the: (1) influence of potential factors on adherence to the BESMILE-HF program, (2) safety of the BESMILE-HF program, and (3) individual experiences and acceptability following the BESMILE-HF program.

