### Quantitative data analysis

Statistical analysis will be performed in a blinded manner by qualified statisticians using PASW Statistics 18.0 (IBM SPSS Inc., Armonk, New York, USA), SAS 9.2 (SAS Institute Inc., Cary, USA), and Stata (Version 13.0, StataCorp). The level of significance will be set at *p* < 0.05. Baseline variables will be reported by groups, descriptively. For the outcome variables, continuous data will be summarized as mean and standard deviation or range, or as median and interquartile range, and categorical data as counts and percentages. The primary analyses for primary and secondary outcome variables will be based on the intention-to-treat population approach, using data collected at baseline and at the 12th week. Differences in terms of outcomes between groups will be compared using an independent *t* test/Mann-Whitney *U* test, as appropriate. For the two co-primary outcomes, the significance level will be Bonferroni-corrected (*α* = 0.05/2 = 0.025). The effect of intervention on outcomes will also be analyzed using multivariate statistical models, with adjustments for baseline score of the outcome variable (where applicable), as well as gender, age, co-morbidities and other variables that are of clinical importance. In addition, multiple imputation methods will be used as a sensitivity analysis to address the issue of missing data. Subgroup analysis will be performed according to gender, cardiac functional classification, left ventricular ejection fraction classifications, and other variables of clinical importance. The secondary analyses for outcome variables will be undertaken as repeated measure analysis and mixed-effects models using all assessment points (4, 8 and 12 weeks). Sensitivity analysis will be performed, including, but not limited to, the analysis for outcome variables using a per-protocol population. Safety will be evaluated by tabulations of AEs, and will be presented with descriptive statistics for each group. A chi-square test or a Fisher’s exact test will be used to compare the frequency difference in AEs between the two groups. To explore potential factors which might influence adherence, a logistic regression model and a linear mixed-effects model will be used and adjusted for potential confounders. Adherence-related data will be taken from exercise log records.

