## Discussion

The EBCR has been recommended in the guidelines for CHF, but it is still in its infancy in China where EBCR services are rare in most regions. The delivery of EBCR should adopt an evidence-based approach, as well as be culturally appropriate and sensitive to individual needs and preferences. The BESMILE-HF study will establish feasibility and provide preliminary evidence on the efficacy and safety of an EBCR program, which will apply *Baduanjin* as the core component in improving exercise capacity and quality of life in patients with CHF. In particular, the BESMILE-HF program has the potential to reach the subgroup of the CHF population with limited physical functional capacity and for whom more intense physical activity is not appropriate.

A limited number of studies have emphasized the importance of individualizing exercise interventions. However, patients’ experience in CHF exercise interventions have not previously been investigated in the Chinese population. This knowledge would help clinicians and researchers in China to gain a context-specific understanding of adherence issues and how standardized interventions could be adjusted to fit individual needs, capacities, and circumstances. Therefore, the BESMILE-HF study will also explore the experience from participants’ perspectives using qualitative research.

Methodological challenges for this study will arise from evaluating a complex intervention as part of EBCR such as (1) training of the whole research team, (2) issues pertaining to the exercise records, and (3) additional physical activity monitoring. Furthermore, due to the nature of intervention, blinding is impossible in this trial. We will make every effort to ensure that outcome assessors, laboratory technicians, data managers, and statisticians are unaware of the treatment allocations.

Altogether, the results of the BESMILE-HF study might provide evidence for how to effectively deliver a contextually adapted EBCR program in China. While this study will lead to conclusions specific to the content, the findings are likely to be relevant for settings with similar lifestyles and demographic profiles, especially those with limited resources.

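### The interview sampling factors do not name adherence or discontinuation, so the acceptability findings may lean towards the views of engaged patients

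*Protocol article*

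**What the plan says.** The last paragraph of the protocol's Background states that the study "aims to assess the efficacy, safety, and acceptability of the addition of the BESMILE-HF program to usual medications for CHF patients in China". The same paragraph lists "individual experiences and acceptability following the BESMILE-HF program" third among the exploratory other objectives. The Design section gives experience and acceptability to Part 2, the semi-structured interviews. The primary and secondary outcome lists contain no acceptability instrument.

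The section *Qualitative data* sets the sampling:

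- Source of interviewees: "Participants who are randomized to the RCT intervention group will be selected for the qualitative study".
- Selection: purposive, on "maximum variation principals regarding age, gender, severity of CHF, education level, working status, whether having grandchildren, and the preliminary results of the pilot study".
- Number: "Participants will be recruited until saturation is reached, and the sample size is expected to be between 15 and 20". Saturation means that a further interview brings no new information.
- Consent: "All participants will provide additional informed consent before taking part in this qualitative study". Interviews last 1 to 1.5 hours, in the hospital or at the patient's home.

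The Discussion says that knowledge of patients' experience would help clinicians and researchers to "gain a context-specific understanding of adherence issues", and gives this as a reason for the qualitative part. Adherence is also studied quantitatively, as a separate objective: "Adherence-related data will be taken from exercise log records". Under *Trial management and quality control*, reasons for withdrawal are recorded if the patient is willing to give them, and the withdrawal rate is analysed.

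**The concern.** Maximum-variation sampling secures spread only on the factors it names. Six of the seven factors here are patient characteristics. The seventh, the pilot results, is left open. How much a patient exercised, and whether the patient stopped, are not named. Yet these are the differences most likely to separate people who found the programme acceptable from those who did not, and they bear directly on the adherence rationale in the Discussion.

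Two features of the plan may add to this. Interviewees must consent a second time to a fairly long interview, which may appeal more to engaged patients. And the saturation rule looks only at the interviews already held: a run of similar accounts from adherent patients can stop yielding new information while the other group remains unheard.

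At stake is the balance of the acceptability themes and of the barriers reported, in a programme that the authors present as a candidate for scale-up in China.

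**Working it through.** **The plan's own figure.** The 15 to 20 interviews are an expectation governed by saturation. There is no formula behind them to reproduce.

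**Reading the rules side by side.** The named factors are age, gender, severity of heart failure, education, working status, having grandchildren, and the pilot's preliminary results: seven in all, none of them adherence, completion or withdrawal. A sample made up only of adherent completers could vary fully on the six patient characteristics and reach saturation. It would then comply with the plan as written, unless the pilot results led the investigators to add a factor.

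**Inputs for an illustration.**

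- 200 patients at 1:1 (*Sample size calculation*; *Randomization, allocation concealment and blinding*), so 100 in the intervention arm.
- About 20% loss to follow-up (*Sample size calculation*), so 0.20 × 100 = 20 lost in that arm if loss is equal between arms. This is only a proxy: low adherers who attend their assessments are not counted as lost, and some lost patients may have left for unrelated reasons.
- k = 15 or 20 interviews (*Qualitative data*).
- r, the rate at which lost patients consent to interview relative to completers. The documents give no value, so r is an assumption, varied from 0.5 to 0.1.

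**Proportional representation.** 0.20 × 15 = 3 and 0.20 × 20 = 4 lost patients expected. For a simple random draw from the arm, the chance of including none is C(80, k)/C(100, k), which is 2.6% for k = 15 and 0.7% for k = 20.

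**Lower consent among lost patients.** Their share of the willing pool is p = 0.2r/(0.2r + 0.8). The expected number is k·p, and the chance of none is approximately (1 − p)^k.

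| r (assumed) | p | Expected, k = 15 / 20 | Chance of none, k = 15 / 20 |
|---|---|---|---|
| 0.5 | 0.1/0.9 = 0.111 | 1.7 / 2.2 | 17% / 10% |
| 0.25 | 0.05/0.85 = 0.059 | 0.9 / 1.2 | 40% / 30% |
| 0.1 | 0.02/0.82 = 0.024 | 0.4 / 0.5 | 69% / 61% |

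Over this range the chance of interviewing no lost patient runs from about 10% to 69%. The table treats selection as random among willing patients, whereas the plan selects purposively. It shows how sensitive the result is to consent and does not forecast this trial.

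**The case against.** The strongest reply is that the plan does not restrict interviews to completers and already contains several safeguards.

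- *Eligibility.* Everyone randomized to the intervention can be selected. A reader might infer from the sampling list that patients who stopped are left out; the text does not say so. What remains is that nothing secures their inclusion.
- *Open seventh factor.* The pilot covers retention, attrition, fidelity and the experience of taking part, so its results could bring adherence into the sampling. This stands: the list is not closed. But it makes no commitment.
- *Other evidence.* Exercise logs are modelled for adherence, withdrawal reasons are sought, and consultations at weeks 4, 8 and 12 discuss difficulties in reaching goals. It would be wrong to infer that the interviews are the only evidence bearing on acceptability. They are the component the protocol names for it, and the other sources do not replace patients' own accounts.
- *Conduct of interviews.* Home interviews reduce the burden, the interviewers are outside the research team, and the questions cover inhibiting influences and challenges. These help with the patients who are interviewed, but not with those who are not.
- *Purpose.* The Discussion's direct aim for the interviews is to explore patients' experience; understanding adherence is part of the rationale. The mismatch is therefore partial.
- *Condensed article.* A full qualitative protocol may hold more detail. However, the article does state its sampling factors, down to having grandchildren, so the comment concerns a stated method.

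**Conclusion.** The point holds as a limited one. The stated sampling factors do not secure variation in adherence or discontinuation, and neither second consent nor saturation makes up for that. The acceptability themes may lean towards favourable views.

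A reader might go further and infer that acceptability will be overstated by some amount, or that about one lost patient will be interviewed. The documents support neither. The content analysis yields themes and no acceptability rate that could be inflated. The figure of about one (0.9 to 1.2) depends on a single assumed consent ratio of one quarter and on loss to follow-up as a stand-in for dissatisfaction. The fair statement is 3 to 4 lost patients under proportional sampling, with a chance of none between about 10% and 69% if relative consent lies between 50% and 10%.

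The co-primary and other efficacy analyses are untouched, and acceptability sits among the exploratory objectives. The weight is modest, but the improvement is cheap.

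**What to change.** In *Qualitative data*, add two items to the maximum-variation factors: level of adherence, taken from the exercise logs, and discontinuation or withdrawal status. State that low adherers and patients who stopped will be actively approached, and report how many were approached and how many interviewed. If few agree, limit the acceptability conclusion to the kinds of patient actually heard.

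Saturation should not depend on a fixed quota of such patients, since that could stall completion of the qualitative part.

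The cost is a change of wording plus some recruitment effort. The logs and withdrawal records are already collected, and the expected 15 to 20 interviews can stay. The downside is that patients who stopped are harder to recruit.
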